### Strategies to improve adherence to interventions {11c}

The treatment intervention under investigation is delivered in a single minimally invasive procedure at day 0 which does not require patient adherence to an intervention throughout the trial.

### Relevant concomitant care permitted or prohibited during the trial {11d}

A concomitant medication log will be used to track all medications (prescription and over-the-counter [OTC]) for each participant. The log will be kept current throughout the participant’s participation in the study and will document the following:Drug nameIndicationStart and stop datesDaily dosage and unit (i.e., mg, mL, tablet)FrequencyRouteReason taken (i.e., adverse event)

A concomitant therapies log will be used to track all therapies (physical therapy, chiropractic care, acupuncture, massage therapy, etc.) for each participant. The log will be kept current throughout the participant’s participation in the study and will document the following:Therapy typeReason for therapyStart and stop datesDuration per sessionFrequency

Participants will be instructed to discontinue pain medications 48 h prior to the procedure. This excludes use of pain medicine other than acetaminophen and/or non-steroidal anti-inflammatory drugs (NSAIDs) for conditions unrelated to DDD.

All concomitant medications and therapies used within the 30 days prior to the screening visit, including medications used for chronic pain symptoms, will be documented on the respective electronic case report forms (eCRFs). Any initiation of new medications or changes to current medications during the course of the study should be recorded on the appropriate eCRF. No other experimental drug or device should be used within 6 months prior to the screening visit or during the course of the clinical trial.

Chronic pain medication including NSAID dosages will be required to remain stable or decrease throughout the trial. Any decreases must be undertaken in consultation with the investigator and documented appropriately in the medical records and appropriate study documents such as the concomitant medication log.

The following concomitant therapies are not permitted during the 24-month study period:Other intradiscal or facet injectionsRhizotomiesSurgery at the same and adjacent vertebral level(s)

If violations of concomitant therapies occur, these will be addressed in the statistical analysis through sensitivity analyses or exclusion from the per-protocol analysis data set.

### Provisions for post-trial care {30}

The participant will be instructed to limit strenuous activity for 72 h and only to perform the normal activities of daily life. After 72 h, normal activity level may be resumed within reason. Strenuous activities including bending, twisting, squatting, or flexing will be avoided until after the post-procedure appointment. Prescriptions may be given to the participant for medications as needed including steroids, muscle relaxers, or narcotic pain relievers. A subgroup of participants may experience moderate to severe pain after the procedure. Oral medications may be needed to treat this post-procedure pain and discomfort. An icepack may be given to the participant to place over the injection site in the event of post-procedure site discomfort.

A study completion form will be completed at the point the participant either completes the protocol-required follow-up or stops participation in the study prematurely to document information and reason for leaving the study including:Study completionLost to follow-upWithdrawal of consent by participantAdverse eventProtocol deviationStudy exit due to other treatmentDeathOther

### Outcomes {12}

The primary efficacy endpoint is the proportion of participants who achieve a minimal clinically important difference (MCID), defined as at least a 30% reduction in back pain VAS score from baseline to 12 months, in the VIA Disc NP group compared to that in the sham control group [8, 9].

The primary safety endpoint will be the proportion of participants that experience one or more treatment-related (investigational product (IP) or procedure) adverse events (AE) in the VIA Disc NP group compared to the sham control group at 12 months.

Additional safety measures will include the following:Proportion of participants who experience an unexpected treatment-related serious adverse eventProportion of participants who experience any AEProportion of participants who experience each unique AE

Secondary efficacy endpoints include:Mean change in VAS score for back pain severity assessed at each follow-up intervalMean change in ODI score for back function assessed at each follow-up intervalProportion of participants who achieve at least a 50% reduction in VAS score for back pain severity (substantial clinical benefit (SCB)) assessed at each follow-up interval [10]Proportion of participants who achieve a patient acceptable symptom state (PASS), defined as a VAS score for pain severity of 30 mm or less, assessed at each follow-up interval [11, 12]Proportion of participants who achieve a MCID, defined as a 30% or greater improvement in ODI score assessed at each follow-up interval [8, 9]Proportion of participants who achieve SCB, defined as a 50% or greater improvement in ODI score assessed at each follow-up interval [13]Proportion of participants who achieve a PASS, defined as a ODI score for back function of 20 or less at all follow-up intervals [14, 15]Proportion of participants in each ODI functional impairment category assessed at each follow-up interval [16]Mean change in EQ-5D-5L score assessed at each follow-up intervalMean PGIC score assessed at each follow-up interval

For participants that have consented to opioid use assessment via prescription drug monitoring program (PDMP):Reductions in opioid use, defined as a ≥ 30% decrease in total dispensed morphine milligram equivalents (MME) from baseline to all follow-up intervals

### Participant timeline {13}

Participants undergo screening and baseline assessments prior to the day 0 procedure. In-person visits are scheduled at months 1, 3, 6, 12, and 24 to collect efficacy and safety data. Phone check-ins at months 9, 15, 18, and 21 gather adverse event and medication updates. The 12-month visit includes crossover evaluation for sham participants (VAS ≥ 40 mm, ODI ≥ 40). All timepoints and procedures follow the protocol schedule of events (Table 1). The participant timeline is shown in Fig. 1.

**Table 1 Tab1:** Schedule of enrollment, interventions, and assessments

Visit/assessment	Screening	VIA Disc NP procedure/randomization	1-Month visit	3-Month visit	6-Month visit	9-Month visit (phone call)	12-Month visit (sham arm crossover)	15-Month visit (phone call)	18-Month visit (phone call)	21-Month visit (phone call)	24-Month visit	Unscheduled visit
	(0–90 days prior*)	(Day 0)	(± 7 days)	(± 14 days)	(± 28 days)	(± 14 days)	(± 45 days)	(± 14 days)	(± 14 days)	(± 14 days)	(± 60 days)	
Informed consent	X^a^											
Eligibility criteria (inclusion/exclusion)	X											
Demographics and back treatment history	X											
Vital signs^b^	X	X										X
Medical history and labs (if applicable)	X											
Urine pregnancy test (for WOCBP)	X	X					X^h^					X^e^
Physical and neurological exams	X	X	X	X	X		X				X	X
MRI and evaluation	X^c^				X							
X-ray (less than or equal to 6 months from screening, AP, lateral, flexion–extension)	X^c^											
VIA Disc NP procedure		X^d^					X^h^					
Oswestry Disability Index (ODI)	X		X	X	X		X				X	
Visual analog scale (VAS)	X		X	X	X		X				X	X
EuroQol-5 Dimension (EQ-5D-5L)	X		X	X	X		X				X	
Patient global impression of change (PGIC)			X	X	X		X				X	
Concomitant medications	X	X	X	X	X	X	X	X	X	X	X	X
Opioid use assessment via PDMP							X					
Concomitant therapies	X	X	X	X	X	X	X	X	X	X	X	X
Adverse events	X	X	X	X	X	X	X	X	X	X	X	X
Study exit							X^g^				X	

*All effort should be made to complete screening within 14 days. Up to 90 days is provided in the event of delays to obtain MRI/MRS

^a^Study procedures must not be performed until after informed consent is signed

^b^Vital signs include oral temperature, sitting blood pressure, pulse oximetry, heart rate, and respiratory rate. On day 0 (day 0 visit), vital signs will be captured both pre- and post-procedure

^c^Participants will undergo MRI and X-rays within 6 months of screening unless site is obtaining advanced imaging, which requires new images. If greater than 6 months or not available, MRI and/or X-rays must be repeated. An MRI of the lower back per the imaging protocol must be obtained within 6 months (+ 28 days) of VIA Disc NP procedure

^d^Participants should be observed for adverse reactions for 30 min post-procedure prior to discharge

^e^Urine pregnancy test should be performed if the participant is a woman of childbearing potential and suspects pregnancy

^g^Participants who do not cross over at 12 months will exit the study

^h^Sham participants with VAS ≥ 40 mm and ODI ≥ 40 may cross over and receive the VIA Disc NP treatment at the 12-month visit

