### Procedure for unblinding if needed {17b}

When it is necessary to break the blind prematurely, the researcher will be required to notify the IRB. The sponsor will be notified as soon as possible, preferably by email or telephone and then in writing, regarding the necessity of code breaking.

Blinded site personnel (e.g., clinical study coordinator, sub-investigators) will record the participant’s PROM scores at the 12-month visit. All participants will then be unblinded to original treatment assignment. Unblinding for purposes of crossover will occur as follows:Participants randomized to the sham control group with VAS ≥ 40 mm and ODI ≥ 40 at 12 months will be approved for crossover to VIA Disc NP treatment and followed for an additional 12 months.Participants in the sham control group with VAS < 40 mm or ODI < 40 at 12 months will be informed that they do not meet the criteria for crossover and will exit the trial.

All participants will proceed unblinded after the 12-month visit to study completion at 24 months.

Emergency unblinding may be necessary if a participant experiences a serious adverse event (SAE) that requires knowledge of the treatment assignment for appropriate medical management. The investigator will contact the designated unblinding contact (e.g., study monitor or medical monitor) to request unblinding. The request for unblinding will be documented, including the reason for unblinding and the date and time of the request. The unblinding contact will access the randomization list and provide the treatment assignment to the investigator. The unblinded information must be treated confidentially and shared only with those necessary for the participant’s safety.

If any blinded party becomes unblinded to treatment allocation for a particular participant, this should be recorded using the unblinding CRF. If a participant is unblinded, they will stay in the trial and be followed up as usual.

Planned unblinding will occur after all primary endpoint data have been collected at the 12-month visit. The process for planned unblinding will be documented in the statistical analysis plan (SAP). The unblinding process will be overseen by the study statistician and data management team. Once unblinding occurs, the treatment assignments will be revealed to the investigators, study team, and participants, as appropriate.

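### As printed, Table 1 gives sham participants injected at month 12 no scheduled contact for about 91 days and no exam or questionnaires for about a year

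*Protocol article*

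**What the plan says.** Table 1 in Participant timeline {13} places the crossover injection in the 12-month column. The column heading names the sham crossover, the procedure and pregnancy-test rows carry a footnoted mark there, and footnote h says that sham participants meeting the pain and disability thresholds "may cross over and receive the VIA Disc NP treatment at the 12-month visit".

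The same section describes the contacts: "In-person visits are scheduled at months 1, 3, 6, 12, and 24 to collect efficacy and safety data", and "Phone check-ins at months 9, 15, 18, and 21 gather adverse event and medication updates". It also states which schedule applies: "All timepoints and procedures follow the protocol schedule of events (Table 1").

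Procedure for unblinding if needed {17b} says that qualifying sham participants "will be approved for crossover to VIA Disc NP treatment and followed for an additional 12 months", and that "All participants will proceed unblinded after the 12-month visit to study completion at 24 months". Trial design {8} calls this a secondary follow-up of 12 months. Both places give a duration and neither gives visit times.

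Provisions for post-trial care {30} contains this instruction: "Strenuous activities including bending, twisting, squatting, or flexing will be avoided until after the post-procedure appointment". Footnote b of Table 1 says: "On day 0 (day 0 visit), vital signs will be captured both pre- and post-procedure". The 30-minute observation in footnote d is worded generally, but its mark appears only in the day-0 cell.

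**The concern.** Crossover participants undergo, for the first time, the same intradiscal injection under sedation that the active arm had on day 0. Adverse event reporting and harms {22} lists its possible harms, among them infection up to discitis or meningitis, epidural bleeding and neurological deterioration. Provisions for post-trial care {30} expects notable pain after the procedure in some participants.

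Table 1 brings day-0 recipients back in person at months 1, 3 and 6. After the crossover injection it brings nobody back before month 24. For the first three months the site would learn of an event only if the participant came forward, and the 24-hour reporting rule for serious events starts only when the site becomes aware. The activity restriction ends at an appointment that, after crossover, Table 1 does not contain.

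**Working it through.** **Inputs, all from Table 1.** Month 1 ± 7 days; month 12 ± 45 days; month 15 (call) ± 14 days; month 24 ± 60 days. One month is taken as 365.25/12 = 30.44 days. The crossover injection is taken to occur at the month-12 visit, as footnote h says.

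**The plan's own figure.** Month 12 to month 24 is 12 × 30.44 = 365 days, which agrees with the additional 12 months stated in {17b}.

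**Which columns apply to a crossover participant.** Under footnote g and {17b}, sham participants who do not cross over leave the study at month 12. Within the sham arm, the columns for months 15 to 24 therefore serve crossover participants only. The three calls are marked for medications, therapies and adverse events. Examination, ODI, VAS, EQ-5D-5L and PGIC are next marked at month 24.

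**Reading A: columns counted from the original day 0.** This anchor is inferred from the column labels and from study completion at 24 months.
- First contact (call): 3 × 30.44 = 91 days. Window limits: 91 − (45 + 14) = 32 to 91 + (45 + 14) = 150 days.
- First examination and questionnaires: 365 days. Window limits: 365 − (45 + 60) = 260 to 365 + (45 + 60) = 470 days.

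**Reading B: the same later columns counted from the crossover injection.**
- First contact (call): 91 ± 14 = 77 to 105 days.
- First examination and questionnaires: 365 ± 60 = 305 to 425 days.

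**Reading C: the month 1, 3, 6, 9 and 12 contacts restart at crossover.**
- First contact, in person: 30 ± 7 = 23 to 37 days. The gap disappears.

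**Day-0 recipient of the same injection.** First scheduled contact after the procedure, in person: 30 days (23 to 37).

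**Scheduled contacts in the 12 months after injection.**

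| | In person | Phone |
|---|---|---|
| Day-0 recipient | 4 (months 1, 3, 6, 12) | 1 (month 9) |
| Crossover recipient, as printed | 1 (month 24) | 3 (months 15, 18, 21) |

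Readings A and B use columns that Table 1 prints after the crossover injection. Reading C needs columns that no text, mark or footnote applies to crossover participants.

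**The case against.** The strongest reply is that a visit-by-visit crossover schedule is the kind of detail a journal article leaves to the full protocol. Fig. 1, the participant timeline, is not available here. The phrase in Trial design {8} about starting a secondary follow-up can be read as Reading C. Two other texts fit that reading: footnote c times an MRI from the VIA Disc NP procedure, with no mark after month 6, and the post-procedure appointment in {30} is worded for participants generally. That section does not name crossover, so applying it there is an inference, although the injection is the same.

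Much of this stands. A reader might infer that the gap exists on any reading of the article. It does not, because Reading C closes it. A reader might also infer that these participants would be left without care for three months. The documents do not support that either: Table 1 has an unscheduled-visit column with vital signs, examination, VAS and adverse events; {11b} promises follow-up and completed safety assessments for all treated participants; and crossover participants know what they received.

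The reply does not make the point vanish. Table 1 is not silent on crossover: it puts the second injection in a named column, and {13} says that the table governs all timepoints. Followed exactly as printed, it gives Reading A or B. Unscheduled visits depend on the participant coming forward.

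**Conclusion.** The point holds for the schedule as printed. The first scheduled contact after a crossover injection is a call at nominally 91 days, and the first examination and questionnaires are at nominally 365 days, against an in-person visit at about 30 days for day-0 recipients. The window ranges above are joint extremes, not typical values. The appointment assumed in {30} has no counterpart in Table 1 after crossover.

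The conclusion rests on two assumptions: that the injection is given at the month-12 visit, and that no separate crossover schedule exists in the full protocol or Fig. 1.

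The consequence is limited to safety follow-up of crossover participants. A reader might infer damage to the trial's main result. The documents do not support that: the primary efficacy and safety comparisons are made at 12 months, and month-12 scores are recorded before unblinding and crossover. The article describes no comparison of crossover with day-0 recipients.

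The number affected is unknown, because no crossover rate is given. As an illustration only, the sham arm would have (248 − 21)/3 = 76 to (446 − 21)/3 = 142 participants if 21 roll-ins are removed from both totals. The article places roll-ins inside the 446 but does not say so for the 248. An assumed crossover rate of 20% to 60% would then give 0.20 × 76 = 15 to 0.60 × 142 = 85 participants, before any loss to follow-up.

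**What to change.** Add a crossover track to Table 1, timed from the date of the crossover injection:

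- one early safety contact at about 1 month, by phone or in person where feasible, named as the post-procedure appointment that ends the activity restriction;
- the three existing calls, re-timed from the injection;
- the final visit at 12 months after the injection;
- vital signs before and after the procedure, and the 30-minute observation, marked for the crossover procedure.

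If the full protocol already restarts the day-0 schedule at crossover, no new visit is needed. State that in Participant timeline {13} and in a footnote to Table 1, with the anchor date.

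The cost is a table amendment and one added contact per crossover participant. It needs no added imaging and does not touch the randomized comparison.

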Participants who meet any of the following criteria will be excluded from participating in this study:Contraindications to the proposed sedation/anesthetic protocolInvolvement of more than two lumbar discs as evidenced by 3 or more discs with a modified Pfirrmann grade of 3 or greaterDisc height of less than 4 mm for any disc between L1 and S1Symptomatic vertebral compression fracturePrevious surgical treatment of the lumbar spineHistory of sacroiliac (SI) joint fusion within the past 6 monthsReceived lumbar epidural or intradiscal steroid injection, lumbar facet-joint steroid injection, lumbar radiofrequency ablation, provocative or anesthetic discography, SI joint pain injection, injection of methylene blue, dextrose, glucosamine, and chondroitin sulfate, or biacuplasty within 3 months of the day 0 procedure. Received intraosseous radiofrequency nerve ablation procedure at the same or adjacent level (e.g., basivertebral nerve ablation or sinuvertebral nerve ablation)Been a recipient of prior intradiscal stem cell/progenitor cell therapy or other biological intervention (e.g., mesenchymal stromal cells [MSC], platelet-rich plasma [PRP]) at the target intervertebral disc within 12 months of the day 0 procedureEvidence of dynamic instability on lumbar flexion–extension radiographs (> 3 mm)Grade 2 or higher spondylolisthesis at the target level, lumbar spondylitis or other undifferentiated spondyloarthropathy, or type III Modic changes adjacent to the target discRadiographic evidence of a full-thickness annular tear at the target disc or other abnormal disc morphologyClinical suspicion of facet pain as primary pain generatorA systemic condition or disease not stabilized or judged by the investigator to be incompatible with participation in the study (e.g., current systemic infection, uncontrolled autoimmune disease, uncontrolled immunodeficiency disease, recent history of myocardial infarction, uncontrolled diabetes (> 7.0% HbA1C))Received VIA Disc NP previouslyDeemed unsuitable for clinical study participation by the investigatorEvidence of substance abuse (including marijuana); note: participants using prescribed extended-release narcotics (e.g., fentanyl patch, MS Contin, oxycontin) within the 3 months prior to screening and participants on long-acting opioids may be given an option to wean off opiates before enrollment; participants on short-acting opiates (e.g., hydrocodone, oxycodone, tramadol) may be included and utilization monitored after the treatmentOpioid use of more than 90 MME/dayCurrently receiving treatment with radiation, chemotherapy, immunosuppression, or chronic steroid therapy (prednisone, or its equivalent, use of up to 5 mg/qd, or inhalation steroids for asthma is allowed)Metal or ceramic implants in the lumbar spine regionContraindications to MRI, including non-MRI compatible devices and active implantable devices such as spinal cord stimulators and intrathecal pumpsInvolved in ongoing or closed (within 6 months of screening visit) litigation related to their back-pain conditionAny mental instability, unstable bipolar disorders, unmanaged post-traumatic stress disorder (PTSD) or uncontrolled anxiety/depression and/or require new or changed anti-depressants or anti-psychotic medications within 3 months of enrollmentDiagnosis of any traumatic neurological disorders that may impact the study as per the judgment of the investigatorWomen who are pregnant or breastfeeding at the time of enrollment and/or plan to become pregnant during the study; pregnancy is confirmed by:A positive pregnancy test during the screening visitSelf-reported pregnancyWomen of childbearing potential (WOCBP) who are not using a reliable form of contraception (as determined by the investigator)Received any experimental drug or device to treat the same condition used within 6 months prior to the screening visit or during the course of the clinical trialOther persistent pain/nerve issues including radiculopathy, leg pain, and cauda equina syndrome

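### The only scheduled baseline VAS and ODI can fall inside the 3-month procedural exclusion, because they are taken at screening while the exclusion is counted back from day 0

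*Protocol article*

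**What the plan says.** **Schedule.** In Table 1 of the protocol article (Participant timeline {13}), VAS and ODI are marked at screening and at months 1, 3, 6, 12 and 24. Their day 0 cells are empty and there is no separate baseline column. The screening column is headed "0–90 days prior". Its footnote sets a target, "All effort should be made to complete screening within 14 days", and then a limit, "Up to 90 days is provided in the event of delays to obtain MRI/MRS". The text of the section mentions baseline assessments before day 0, names no other visit for them, and says: "All timepoints and procedures follow the protocol schedule of events (Table 1").

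**Endpoint.** Outcomes {12} makes the primary endpoint a responder proportion, "defined as at least a 30% reduction in back pain VAS score from baseline to 12 months". Several secondary endpoints are also changes from baseline in VAS or ODI.

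**Exclusions.** Eligibility criteria {10} excludes a list of injections, ablation, discography and "biacuplasty within 3 months of the day 0 procedure". In the same list, participants on long-acting opioids "may be given an option to wean off opiates before enrollment".

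**Randomisation.** Sequence generation {16a} places it at the day 0 visit, once every eligibility criterion has been evaluated.

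**The concern.** An exclusion for recent procedures helps a pain endpoint only if the pain score is taken after the excluded interval has run. Here the interval ends at day 0, while the score that serves as the denominator of the primary endpoint is taken earlier. A participant can satisfy every criterion and still have a baseline recorded while a recent procedure is affecting pain.

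If that baseline is lower than the settled level, the 30% target becomes harder to reach; if it is higher, the target becomes easier. Either way, the responder label no longer describes change from the state at treatment. The analysis cannot repair this later, because a pre-treatment value that was never collected cannot be recovered.

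**Working it through.** **1. The plan's own figures.** Sample size {14} uses a pooled Z-test, 85% power, one-sided alpha 0.025 and 2:1 allocation. The control-arm size is

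n_C = [1.960·√(1.5·p̄(1−p̄)) + 1.036·√(p_C(1−p_C) + p_T(1−p_T)/2)]² / (p_T − p_C)², with p̄ = (p_C + 2p_T)/3 and total N = 3·n_C.

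- 40% v 60%: N = 248.3 (stated 248; power at 248 is 85.0%).
- 40% v 55%: N = 444.2 (stated 446; power at 446 is 85.1%).

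The stated sizes reproduce. This point does not change them.

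**2. Timing.** Let I be the day of the excluded procedure and S the day of the screening VAS, both in days before day 0. Let W be the 3-month interval, taken as 91 days (the article does not convert months to days).

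- Passes the exclusion if I > W.
- Time from procedure to baseline is I − S.
- Baseline lies inside the interval if I − S < W, that is, if I < W + S.

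Every participant with W < I < W + S is therefore eligible and has a baseline inside the interval.

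| S (screening VAS) | I (procedure) | Passes (I > 91) | I − S |
|---|---|---|---|
| 90 (limit) | 92 | yes | 2 days |
| 88 | 93 | yes | 5 days |
| 14 (target) | 92 | yes | 78 days |

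With W = 90 or 92, the shortest gap at the 14-day target is 77 or 79 days. No deviation from the protocol is needed in any row.

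**3. Effect on one participant's endpoint.** The response cut-off is 0.70 × baseline VAS. The VAS values below are assumed for illustration.

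- Settled 75 mm, screening 45 mm: the cut-off is 0.70 × 45 = 31.5 mm instead of 0.70 × 75 = 52.5 mm. A month-12 VAS of 50 mm is a failure, although it is (75 − 50)/75 = 33% below the settled level.
- Settled 60 mm, screening 50, 45 or 40 mm: cut-offs are 35, 31.5 and 28 mm. These need falls of 41.7%, 47.5% and 53.3% from the settled level instead of 30%.
- Opposite direction, settled 50 mm and screening 60 mm: the cut-off is 42 mm, so a 16% fall is enough.

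The entry floor of 40 mm limits the first direction: no baseline can give a cut-off below 0.70 × 40 = 28 mm.

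**4. What dilution would cost.** Suppose a share f of participants contributes no treatment difference. The treatment rate becomes 0.40 + (1 − f)(p_T − 0.40).

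| f | Power, N = 248 (40% v 60%) | Power, N = 446 (40% v 55%) |
|---|---|---|
| 0 | 85.0% | 85.1% |
| 5% | 81.1% | 81.3% |
| 10% | 76.6% | 77.0% |
| 20% | 66.4% | 66.9% |

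The article gives no value for f, and total loss of the difference in affected participants is a harsh assumption. The table shows sensitivity only; it is not an estimate.

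**5. Opioid weaning.** The wean is tied to 'enrollment', which the article does not define. Sample size {14} uses 'enrolled' for the subjects counted in the comparison, and randomisation is on day 0. On that reading, a participant may wean after the screening VAS. If enrollment means consent, the wean comes before the screening VAS and the problem disappears. The passages need to be reconciled.

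**The case against.** **Points that limit the concern.** The 90 days are an allowance for imaging delays, with 14 days as the target. Screening is a window, and nothing puts the VAS on its first day. The worked case combines a late day 0, a recent injection and a large temporary effect that still leaves VAS and ODI at 40 or above. The article condenses a fuller protocol, its Figure 1 is not shown, and baseline may be defined elsewhere. All this makes the affected share uncertain and perhaps small. It does not remove the gap: the schedule is printed with its footnotes, the text defers to it, and the gap remains at the 14-day target.

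**Stronger readings that the document does not support.**

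- *Bias between arms or type I error inflation.* A reader might infer this. Allocation is randomised after the baseline, and participants and assessors are blinded to month 12, so the error should be similar in both arms.
- *Eligibility is never checked after screening.* Table 1 marks eligibility only there, but Sequence generation {16a} requires all criteria to be evaluated before randomisation on day 0. The interval from a past injection to day 0 is simple date arithmetic.
- *Weaning is timed to day 0.* The text says enrollment, and nowhere says that all follow-up is off opioids.
- *The 12-month exclusion for prior biologics is equally exposed.* At worst the baseline falls about 9 months after the biologic, and the article shows no effect on VAS at that distance.
- *Ordinary VAS drift gives the size.* Assume mean 55 or 62 mm, SD 18, correlation 0.5 to 0.8 and no treatment effect. Then 4.2–16.3% would meet the 30% criterion by chance from a screening baseline, against 3.6–14.7% from a day 0 baseline re-tested against the 40–90 mm limits. The change is only 0.6–1.7 points. This models normal variation between readings, not a recent procedure or a wean, so it does not measure this problem.

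**Conclusion.** The point holds for the 3-month procedural exclusion. As written, the only scheduled pre-treatment VAS and ODI can fall inside that interval in a fully compliant participant, by as much as a baseline 2 days after the procedure at the 90-day limit. It holds conditionally for opioid weaning, depending on the meaning of enrollment.

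The consequence is non-differential misclassification of responders and some dilution of the difference. Absolute responder rates also become harder to interpret. The total effect cannot be estimated, because the article does not say how many participants will screen early after a procedure or wean after screening. The timing result rests on 3 months being about 91 days and on Table 1 being the complete schedule. A cheap correction is worthwhile, and it is time-sensitive because enrolment began in July 2025.

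**What to change.** Amend Table 1 to add VAS and ODI shortly before randomisation, for example within 14 days before day 0. Take them after the 3-month interval and any wean are complete, and before the 48-h analgesic stop begins. Define that value as baseline for the primary endpoint and the secondary VAS and ODI change endpoints. If the screening value already meets these conditions, it stands.

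Two details need a sentence each:

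- For a procedure only just over 3 months before day 0, no day may lie both after the interval and before the 48-h stop. The sponsor should state in advance how baseline is taken then, for instance on day 0 before randomisation, with the analgesic stop recorded.
- Define 'enrollment' in the weaning note, so that its order relative to the baseline VAS is clear.

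Whether to re-apply the VAS and ODI entry limits to the repeat value is a trade-off for the sponsor (late screen failures against a cleaner population), and the fix does not depend on it. The length of the exclusion and the weaning option are left as they are.

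Cost: two questionnaires already in use, repeated for some participants, and a schedule amendment. The sample size is unchanged.
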